### Outcomes

#### Primary outcomes of the RCT

The trial has two primary study outcomes that will be used to assess the impact of the prenatal and the postnatal intervention, respectively:

Incidence of SGA, defined as birth weight <10th centile of the Intergrowth 21st reference.^29^Length-for-age z-score (LAZ) calculated using the WHO 2006 growth reference at 6 months of age.^30^

#### Secondary outcomes of the RCT

A list of the trial’s secondary outcomes can be found in table 2.

**Table 2 T2:** Secondary outcomes of the RCT on maternal, newborn and child level

Maternal outcomes	Newborn	Child
Total and trimester-specific prenatal weight gain and gestational weight change.	Birth weight (measured within 72 hours after birth).	Weight-for-age Z-score at 6 months of age (WAZ) (and 9 and 12 months on a subsample).
Probable and possible maternal postnatal depression at 2 and 6 months of child age.	Birth length (measured within 72 hours after birth).	Weight-for-length Z-score at 6 months of age (WLZ) (and 9 and 12 months on a subsample).
Maternal anaemia at the third antenatal consultation.	Ponderal or Rohrer’s index at birth.	Stunting at 6 months of age.
Women’s mean and minimum dietary diversity score (measured twice weekly).	Gestational age at delivery.	Wasting at 6 months of age.
	Large-for-gestational age.	Underweight at 6 months of age.
	Chest circumference (measured within 72 hours after birth).	Duration of exclusive breastfeeding during the first 6 months of age.
	Head circumference (measured within 72 hours after birth).	Incidence of child wasting over first 6 months of life.
	Arm circumference (measured within 72 hours after birth).	Weight gain over first 6 months of life.
	Incidence of preterm birth.	Child mortality (between birth and 6 months of age).
	Fetal loss.	Monthly change in LAZ over first 6 months of life.
	Stillbirths.	Monthly change in WLZ over first 6 months of life.
		Monthly change in WAZ over first 6 months of life.
		Monthly change in head circumference over first 6 months of life.
		Child morbidity symptoms over first 6 months of life.
		Anaemia at 6 months of age.
		Haemoglobin concentration at 6 months of age.

LAZ, length-for-age z-score; RCT, randomised controlled trial.

Birth weight measurements will be defined using the Intergrowth 21st reference,^29^ and child anthropometry will be defined using the Child Growth Standards developed by the WHO.^30^

#### Outcomes of the substudies

Substudy 1: impact of the intervention on neonatal and maternal body composition 2–3 weeks after delivery.

Body composition will be determined in mother–child dyads by deuterium dilution and analysis of saliva by a Fourier Transform Infrared reader (Agilent FTIR 4500 series). The substudy will also assess if early gestation maternal BMI (defined as body weight in kilograms divided by the square of height in metres) modifies the intervention’s effect on neonatal body composition.

Substudy 2: impact of the intervention on dietary intake.

A dietary assessment study will be conducted, using a 24-hour dietary recall in a subsample of women. This substudy will enable us to assess possible substitution of the prenatal diet by the BEP supplement.

Substudy 3: impact of the intervention on breastmilk.

Breastmilk samples will be taken in the four study groups to compare the composition and to analyse the interaction between the supplementation periods.

### Sample size

With an SGA prevalence of 32% and an anticipated decrease of 7%, a sample of 652 subjects per prenatal arm is required with α=0.05 and β=0.2.^26^ To accommodate for possible losses, the number of subjects per arm was increased to 888 (total subjects: 1776). Possible losses are based on previous MISAME studies where the prevalence was ~26 % due to a combination of miscarriage, stillbirths, multifetal pregnancies, outmigrants, maternal deaths and incomplete data.^18^ For the analysis of an effect of the postnatal intervention on LAZ at 6 months of age, the minimally detectable effect depends on the presence or absence of an interaction effect between the prenatal and postnatal intervention. In the absence of a statistically significant interaction between prenatal and postnatal intervention, at sample size of 588 children per postnatal study arm would allow us to detect a difference of 0.18 Z-score (SD=1.1) based on a cross-sectional survey conducted in the Gourcy health district in Burkina Faso,^31^ between study arms with α=0.05 and β=0.20. This implies that if ~1400 singleton live births are available, we allow for a maximum loss to follow-up of 16%. In the presence of a statistically significant interaction between prenatal and postnatal intervention, a total sample size of 1176 represents 294 children per factorial combination of the prenatal and postnatal study group (four groups in total). A subgroup size of 294 would allow us to detect a difference in LAZ at 6 months of age of 0.28 assuming an SD of 1.1, α=0.025 (Bonferroni correction for two primary endpoints analyses) and β=0.20.

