**Trial registration number:**

NCT03533712.

Strengths and limitations of this studyThis trial will help to fill the evidence gap on the effect of balanced energy-protein (BEP) supplements in pregnant and lactating women on birth outcomes and infant growth.Formative research to select the most suitable BEP supplement ensured that the selected BEP is well accepted by the study population.The daily intake of BEP supplements and iron/folic acid tablets during pregnancy and lactation will be directly observed by study workers.This study will assess the impact of factorial combinations of prenatal and postnatal BEP on child growth to elucidate the relative importance of BEP during pregnancy and/or early lactation.Blinding of study participants and staff members will not be possible, as the supplements are identifiable.

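### A significance test for interaction chooses the primary postnatal LAZ comparison, and the α and power printed for each branch ignore that selection step

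*Protocol article*

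**What the plan says.** LAZ at 6 months is the primary outcome for the postnatal intervention (Primary outcomes of the RCT). The Sample size section says that the detectable difference depends on whether the prenatal and postnatal interventions interact, and then gives two cases.

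- Interaction not significant: the two postnatal arms are compared with the prenatal groups pooled. The condition reads "In the absence of a statistically significant interaction between prenatal and postnatal intervention, at sample size of 588 children per postnatal study arm", and the claim attached to it is "588 children per postnatal study arm would allow us to detect a difference of 0.18 Z-score (SD=1.1", "between study arms with α=0.05 and β=0.20".
- Interaction significant: "In the presence of a statistically significant interaction between prenatal and postnatal intervention, a total sample size of 1176 represents 294 children per factorial combination". For these cells it says "A subgroup size of 294 would allow us to detect a difference in LAZ at 6 months of age of 0.28", with "α=0.025 (Bonferroni correction for two primary endpoints analyses) and β=0.20".

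No significance level or power is given for the interaction test, and no effect is assumed for the other prenatal stratum. The Statistical analysis section refers to a separate plan that is not shown. The strengths and limitations box presents the factorial question as a feature of the trial: "This study will assess the impact of factorial combinations of prenatal and postnatal BEP on child growth".

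**The concern.** A detectable difference can change with a test result only if the analysed contrast changes with it. As printed, then, the same data first decide which LAZ contrast is primary and are then used to test that contrast. This raises two problems.

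First, the rule can make a false postnatal claim by either route, so its overall error rate is not the α printed for either branch.

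Second, the 80% for 0.28 takes the subgroup branch as given, although the trial must first obtain a significant interaction. An interaction contrast in a 2×2 design has twice the standard error of the marginal contrast, so that test is weak here. A non-significant result is poor evidence that the postnatal effect is the same in both strata, yet it would send the trial to the pooled comparison. Whether the postnatal conclusion is general or specific to one prenatal group would then rest on a low-powered test of unstated level.

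**Working it through.** **Inputs (Sample size section).** 588 per postnatal arm; 294 per cell; SD 1.1; α 0.05 (pooled) and 0.025 (cells); β 0.20. Tests are taken as two-sided, which is not stated but reproduces the printed figures. The level of the interaction test is an assumption: 5%, with 10% to 20% as a range. Normal approximation with known SD.

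**1. The printed figures, each branch taken as fixed.**
- Pooled: (1.960 + 0.842) × 1.1 × √(2/588) = 0.180. Power for 0.18 is 80.1%.
- Cells: (2.241 + 0.842) × 1.1 × √(2/294) = 0.280. Power for 0.28 is 80.1%.

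Both reproduce.

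**2. Standard errors.**
- Simple postnatal effect within a prenatal stratum: 1.1 × √(2/294) = 0.0907.
- Marginal postnatal effect: 1.1 × √(2/588) = 0.0642.
- Interaction (difference between the two simple effects): 1.1 × √(4/294) = 0.1283.

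A 5% interaction test has 80% power only for 2.802 × 0.1283 = 0.36, twice the 0.18 used for the pooled comparison.

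**3. Type I error of the rule, no postnatal effect in either stratum.** With equal cells the interaction and marginal estimates are independent. For a 5% interaction test:
- Pooled route: 0.95 × 0.05 = 4.75%.
- Subgroup route: P(interaction significant and at least one simple effect significant at 0.025) = 2.1%, by numerical integration.
- Total: about 6.9%.

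With the interaction tested at 10% the total is about 7.5%, and at 20% about 7.8%. If the pooled test also used 0.025, the total would be 4.5% (5% interaction test) or 5.2% (10%).

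**4. Chance of finding a 0.28 effect through the subgroup branch (5% interaction test).** With 0.28 in one stratum and 0 in the other:
- P(interaction significant) = Φ(0.28/0.1283 − 1.960) = Φ(0.222) = 58.8%.
- P(interaction significant and the 0.28 comparison significant at 0.025) = 55.6%.
- P(pooled claim instead) = (1 − 0.588) × 0.588 = 24.2%. Here the marginal effect is 0.14, and its power is Φ(0.14/0.0642 − 1.960) = 58.8%.
- P(any significant postnatal finding) = about 80%.
- Power for 0.28 given a significant interaction = 0.556/0.588 = about 95%.

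The joint probability depends heavily on the other stratum:

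| Effect in other stratum | 0.28 found through subgroup branch | Pooled claim instead |
|---|---|---|
| 0.14 | 19% | 73% |
| 0 | 56% | 24% |
| −0.14 | 77% | 2% |
| −0.28 | 80% | under 0.1% |

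With 0 in the other stratum, raising the interaction level to 10% or 20% gives about 65% or 72%.

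**The case against.** **The rule is inferred from sample-size text.** The section does not name the primary contrast, the level of the interaction test or which cells are compared, and the analysis plan is not shown. That plan may fix a single contrast. This limits how firmly the procedure can be attributed to the trial. It does not remove the point, because the conditional rule and its figures are printed in the article. If the analysis plan fixes one contrast, the Sample size section misdescribes the trial and needs the same correction.

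**The 80% is not miscalculated.** This stands. A reader might infer that the true power for 0.28 is 56%. The documents do not support that. The 80% is right for a two-cell comparison fixed in advance, and in the 0.28/0 case power given a significant interaction is higher still. The 56% is a different quantity, the joint chance of passing both tests. It needs an interaction level and an other-stratum effect that the article does not give.

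**The error inflation depends on the pooled test being run at 0.05.** The 0.025 is labelled as a correction for two primary endpoints, so it could have been meant for the pooled test too, and the rule would then run at about 4.5% to 5.2%. But 0.05 is what the section prints for that branch. With 0.025 there, power for 0.18 would be about 71%, not the stated 80%.

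**The two-stage rule has an advantage.** If only one stratum benefits, it yields some postnatal finding about 80% of the time, against 59% for the marginal test alone. This stands and belongs in the cost of the fix.

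**Conclusion.** The point holds as a badly fixed rule in the Sample size section and should be fixed. The printed α levels are not the error rate of the rule as printed. With no postnatal effect in either stratum, that rate is about 6.9% to 7.8% for interaction tests at 5% to 20%, assuming two-sided tests, both simple effects tested at 0.025 and the pooled test at 0.05. The inflation is modest, and it barely depends on the level assumed for the interaction test.

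On power, the defect is a missing qualification, not an arithmetical error. The 80% for 0.28 holds only for a cell comparison chosen beforehand. Under the two-stage rule with a 5% interaction test, the chance of reaching and detecting that effect runs from 19% to 80% over the other-stratum effects examined. No single figure, 56% included, should be quoted as the power of the design.

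**What to change.** 1. Name the marginal postnatal contrast (prenatal groups pooled, adjusted for prenatal allocation) as the primary LAZ analysis at the α printed for it, 0.05, whatever the interaction test shows.
2. Report the prenatal-by-postnatal interaction with its 95% CI, and the simple effects within prenatal groups, as secondary. State that a 5% interaction test has 80% power only at about 0.36 z.
3. Keep the 0.28 figure only with the statement that its 80% applies to a prespecified cell comparison and does not account for the interaction test.
4. Make the Sample size section and the analysis plan agree on these points before outcome data are seen.

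This restores the 5% level for the primary LAZ claim and keeps 80% power for 0.18. It changes wording only, with no change to sample size or conduct. The statistical cost should be stated openly: if the effect is 0.28 in one stratum and 0 in the other, the marginal test has about 59% power, against about 80% for any postnatal finding under the two-stage rule.

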### Data collection

#### Anthropometric and clinical procedures

At enrolment, anthropometric measurements from all women will be taken. Gestational age will be determined during an ultrasound consultation by measuring crown-rump length (7–13 weeks) or by calculating the mean of three to four measurements: biparietal diameter, head circumference, abdominal circumference and femur length (12–26 weeks).^32^

During pregnancy, clinical follow-up will consist of antenatal visits following the national guidelines.

At birth, anthropometric measurements of all neonates will be assessed in duplicate within the first 72 hours of life (in practice, the aim is to measure within the 24 hours of life). After birth, mother and child will visit the healthcare centres monthly for a follow-up on clinical, anthropometric and child morbidity measures (signs including fever, vomiting, diarrhoea, cough, difficulty breathing and running nose). A subsample will be measured at the healthcare centres or at home by the project interviewers to collect postnatal data at months 9 and 12.

Haemoglobin concentrations will be measured in women at enrolment and during the third antenatal care visit. This will be conducted at 6 months of age among children.

#### Baseline questionnaires

Prenatal and postnatal maternal depression will be assessed using the standardised Edinburgh Postnatal Depression Scale questionnaire consisting of 10 questions.^33^ Project midwives will be trained for this, and the questionnaire will be asked at inclusion and at months 2 and 6 after birth. Socioeconomic and demographic information from all participants will be collected once included. Trained project interviewers will ask questions on household members’ characteristics, household properties, WASH environment and household food security.^34^ The women’s dietary diversity score will be measured in all participating women by the FA during the home visits. This will be enumerated twice a week per participant using the Women’s Dietary Diversity Score with 11 food groups.^35^

Table 3 shows the overview of the time schedule and measurements of the trial.

**Table 3 T3:** Participant timeline schedule of enrolment, interventions, assessment and visits

	Enrolment		Allocation	Postallocation											
				Pregnancy and birth				After birth							
	Start	5- weekly visits	ANC 1	Household visit	Ultrasound	ANC 2, 3 and 4	Birth	Month 1	Month 2	Month 3	Month 4	Month 5	Month 6	Month 9	Month 12
**Enrolment**															
Census	×														
Pregnancy identification		×													
Pregnancy confirmatory test			×												
Informed consent and allocation to study group			×												
**Study groups**															
Prenatal BEP+IFA			x  x												
Prenatal IFA			x  x												
Postnatal BEP+IFA*							x  x								
Postnatal IFA							x  x								
**Assessments**															
**Mothers**															
Baseline questionnaire				×											
Gestational age determination					×										
Skinfold measurements					×										
Weight (kg) and arm circumference (mm) †/‡			×			×	×	×	×	×	×	×	×	×	×
Height (cm)			×												
Haemoglobin (g/dL)			×			× (ANC3)									
Women’s Dietary Diversity Score (twice weekly)				×											
Maternal depression			×						×				×		
**Infants**															
Birth weight (kg)							×								
Birth length (cm)							×								
Head circumference (mm)							×	×	×	×	×	×	×		
Chest circumference (mm)							×								
Arm circumference (mm)							×	×	×	×	×	×	×	×	×
Morbidity								×	×	×	×	×	×		
Mortality							×	×	×	×	×	×	×		
Weight (kg) and height (cm)								×	×	×	×	×	×	×	×
Breastfeeding practices								×	×	×	×	×	×		
Haemoglobin (g/dL)													×		

*The IFA tablets will be given during the first 6 weeks after birth in the postnatal intervention group, according to the national health protocol.

†Only maternal weight will be taken at birth.

‡In a subsample at months 9 and 12.

BEP, balanced energy–protein; IFA, iron/folic acid.

Quality of all study data will be insured by a thorough training of all field staff. Procedures to handle data collection tools (questionnaires, anthropometric and clinical measurement material, and laboratory procedures) will be pretested in the field during a dry-run of ±3 months. Anthropometric measurement standardisations of the field staff will be repeated bimonthly throughout the trial. Anthropometric measurements will be taken in duplicate. Newborns will be measured within 72 hours after birth (preferably within the 24 hours), and all weighing scales and HemoCue 201+ devices will undergo weekly quality control. A WhatsApp group will be set up where problems can be communicated and solved quickly.

All data collection forms of the trial can be found on: www.misame3.ugent.be

Women will be designated as lost to follow-up if they move from the study area or withdraw their participation. Reasons for discontinuation will be recorded.

Women will be enrolled in the study from October 2019 until the total sample size has been reached.

### Data management and analysis

FAs will use smartphones with computer-assisted person interviewing programmed in CSPRO (version 7.3.1) to collect data during household visits. The study data collected by the project medical doctor, project midwives and interviewers will be done by Survey Solutions data entry software (V.19.12.6) on tablets. This data will be uploaded to a central server on a weekly basis. All questionnaires were programmed and have been tested on the Survey Solutions Designer website and include validation codes to promote the quality of the data entry in the field. Assignments will be sent once a week to the tablets of the field team, and preloaded data collected at an earlier contact moment will be used to lower the amount of incorrect data. Paper forms will also be available on the field as a backup.

Further data quality checks will be conducted in Stata V.14.2 (Statacorp, Texas, USA). Missing or inconsistent data outliers will be sent back to the field for revision.

### Statistical analysis

We refer to the Statistical Analysis Plan of the trial ‘*Statistical analysis plan: Impact of a prenatal and postnatal balanced energy-protein supplement on birth size and postnatal child growth in Burkina Faso*’ published on: www.misame3.ugent.be

### Data monitoring

#### Data monitoring and auditing

The Data and Safety Monitoring Board is an independent multidisciplinary group whose members are not involved in the trial. The board consists of a Belgian endocrinologist, a Belgian paediatrician, a Burkinabè paediatrician, a Belgian gynaecologist and a Belgian ethicist.

#### Serious adverse events (SAEs)

FAs will be trained to recognise health issues and will actively refer those participants to see the project midwife in the primary health facilities or Centre de Santé et Promotion Sociale (CSPS) in the event they occur. All SAEs will be recorded on a case-by-case basis, and verbal autopsies will be conducted for maternal, neonatal and infant deaths by the field medical doctor.

## Ethics and dissemination

### Ethics approval and consent to participate

MISAME-III has been reviewed and approved by the University Hospital of Ghent University (B670201734334) and the Burkinabe ethics (N°2018–22/MS/SG/CM/CEI) committee. Important protocol changes will be noted on ClinicalTrials.gov. When eligible women meet the inclusion criteria, project midwives will explain the background and procedure of the complete trial. Written informed consent or assent will be asked from the participating women. In case of illiteracy, a thumb print will be asked and witnessed by the recruiting investigator and one extra witness. Participants will be told that all data collected during the trial is confidential and that they are allowed to withdraw at any time. A copy of the informed consent and assent can be found on www.misame3.ugent.be and as supplementary file (online supplemental file 2).

10.1136/bmjopen-2020-038393.supp2Supplementary data

### Patient and public involvement

MISAME-III has been well accepted by the community, because of the previous positive experiences they had with the MISAME-I and II studies. Through the formative study, women were involved in the choice of BEP supplement. Workshops will be planned at the end of the study in order to communicate the study results to the community.

### Ancillary care

The MISAME-III project will pay for ancillary care when participants have health issues and in case the costs are not covered by the national healthcare programme. Participants suffering harm due to their trial participation will be covered.

### Confidentiality

A data management plan has been put in place to address concerns regarding the General Data Protection Regulation rules. During the trial, the data files containing personal identifying information will be stored on the Survey Solutions server. Only the principal investigators and the project coordinators will be able to access those files.

### Dissemination plan

On completion of the trial, all anonymised study data will be available on request. Final results will be communicated to the participants, the Burkinabè Ministry of health, the field staff, the BMGF, Ghent University researchers and students, AFRICSanté, healthcare professionals and other relevant international public institutions. Papers on the study results will be published in peer-reviewed journals and will be available on the project website. All investigators contributing to the realisation of the project and publication of results will be included as an author. Other contributors such as the participants, FA and field staff members will be mentioned in the acknowledgements.

MISAME-III has been well accepted by the community, because of the previous positive experiences they had with the MISAME-I and II studies. Through the formative study, women were involved in the choice of BEP supplement. Workshops will be planned at the end of the study in order to communicate the study results to the community.

